**Fig. 2 Fig2:**
[figure not shown]
Schedule of enrollment, interventions, and assessments. Abbreviations: *ATS* Attention Test Scale, *MRI* magnetic resonance imaging, *PAS* Pain Assessment of Sphygmomanometer, *SAS* Self-rating Anxiety Scale, *SDS* Self-rating Depression Scale, *SF-12* 12-Item Short Form Health Survey, *WOMAC* Western Ontario and McMaster osteoarthritis index

### Randomization

Eligible patients will be randomly assigned in a ratio of 1:1:1 to the celecoxib group, placebo group, and waiting list group with 36 patients in each group. Random number lists will be created in accordance with PROC PLAN of SAS 9.2 (SAS Institute Inc., Cary, NC, USA). The randomization allocation will use sequentially numbered, opaque, and sealed envelopes by an independent assistant. The celecoxib group and the placebo group will be concealed from the researchers until completion of the statistical analysis.

### Blinding

As waiting list group without any medical intervention, while the other two groups will be given celecoxib or placebo 200mg daily, it is impossible to blind the patients, clinicians and investigators totally. Patients and researchers of the celecoxib group and the placebo group will be unaware of the assignments until completion of the statistical analysis. Only an independent researcher in the pharmacy department knows the allocation of the celecoxib and placebo groups. The evaluators and statisticians will be blinded to the group allocation during outcome evaluation and data analysis to reduce the risk of bias.

### Interventions

Patients in the celecoxib group will orally take a celecoxib capsule (approval number J20030098, manufactured by Pfizer Pharmaceutical Co. Ltd., Beijing, China) at a daily dosage of 200 mg for 2 weeks. Patients in the placebo group will receive a placebo capsule (manufactured by pharmacy department of Affiliated Hospital of Chengdu University of TCM) with oral administration at the same dosage as celecoxib capsule once a day for 2 weeks. The placebo capsule is identical in appearance, smell, and texture to the celecoxib capsule. Patients in the waiting list group will be observed for 2 weeks without any medical or other interventions. After 2 weeks’ observation, patients in the waiting list group and placebo group could choose either 2 weeks’ celecoxib treatment or acupuncture treatments free of charge.

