### Outcome measurement

The clinical evaluations will comprise four components: knee pain, knee function, cognition, and emotion. All evaluations will be performed twice: at baseline and after 2 weeks’ intervention or observation. All evaluations will be evaluated by two trained licensed physicians.

The primary outcome measurements are VAS and the short form of the McGill pain questionnaire of average knee pain in the last 2 weeks and the VAS of knee pain during the MRI scan. The short form of the McGill pain questionnaire could measure the sensory and affective component of pain.

The secondary outcome measurements are the Western Ontario and McMaster Universities Osteoarthritis Index (WOMAC) [27], Attention Test Scale (ATS), Pain Assessment of Sphygmomanometer, Self-rating Anxiety Scale (SAS), Self-rating Depression Scale (SDS), and 12-Item Short Form Health Survey (SF-12). WOMAC could help measure the pain, knee joint function, and quality of life of patients with KOA.

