### Trial status

The trial is currently in the participant recruitment stage. The trial began recruitment on October 18, 2017 and is expected to be complete on December 31, 2019. This trial is reported in the light of the Standard Protocol Items: Recommendations for Intervention Trials (SPIRIT) guidelines (Additional file 1), [38].

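### The treatment choice after the 2 weeks goes to placebo patients but not celecoxib patients, so the promise to blind both capsule groups until the analysis is complete fails unless the offer waits until then

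*Protocol article*

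**What the plan says.** Three sections of the protocol article bear on this point.

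- **Interventions.** After the 2 weeks, "patients in the waiting list group and placebo group could choose either" a further 2 weeks of celecoxib or acupuncture, at no cost. The celecoxib group is not included.
- **Blinding.** "Patients and researchers of the celecoxib group and the placebo group will be unaware of the assignments until completion of the statistical analysis". The code is closely held: "Only an independent researcher in the pharmacy department knows the allocation of the celecoxib and placebo groups". A separate sentence covers assessors and analysts: "The evaluators and statisticians will be blinded to the group allocation during outcome evaluation and data analysis to reduce the risk of bias".
- **Randomization.** The commitment is repeated for staff: "The celecoxib group and the placebo group will be concealed from the researchers until completion of the statistical analysis".

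The Blinding section also concedes that "it is impossible to blind the patients, clinicians and investigators totally", but it gives the untreated waiting list as the reason and then makes the unqualified promise for the two capsule groups.

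On timing, Outcome measurement states: "All evaluations will be performed twice: at baseline and after 2 weeks" of intervention or observation. Trial status states: "The trial began recruitment on October 18, 2017 and is expected to be complete on December 31, 2019".

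**The concern.** An offer made to one of two blinded groups and not the other discloses the allocation. Celecoxib versus placebo is the only contrast in this trial that can be blinded, and the primary outcomes are patient-reported pain scales, so the blinding claim carries much of the credibility of that comparison.

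Two things are at stake. The first is the truth of the claim: a report that patients and researchers were unaware of assignment until the analysis was finished would be wrong if the offers were made along the way. The second is the gradual unblinding of research staff. Under Data analysis, the research group gives the statisticians a scheme setting out the data needed and how they are to be processed. The Sample size section also expects losses from excessive head motion. If people who learn assignments through the offers take part in those decisions, they make them knowing the code.

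**Working it through.** No figure in the plan is to be reproduced. The check sets the statements side by side.

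1. **Who receives the offer.** Waiting list: yes. Placebo: yes. Celecoxib: not named (Interventions).
2. **What the offer reveals.** Waiting-list patients already know their group, so nothing new is disclosed there. Among capsule patients, one who is offered the choice was on placebo, and one who is passed over was on celecoxib.
3. **To whom it is revealed.**
   - *Placebo patients.* They learn their own assignment if they know, or are told, which groups the offer is for.
   - *Whoever administers the offer.* That person must know which capsule patients qualify, and so knows both groups: 36 placebo + 36 celecoxib = 72 planned patients.
   - *Celecoxib patients.* They can infer their group only if they know that the offer exists for others. The Informed consent section does not say whether they are told.
4. **Against the code-holding statement.** Only the pharmacy researcher knows which capsule is which. The offer therefore cannot be directed to placebo patients unless that person makes it or releases the code.
5. **When it happens.** Recruitment began on 18 October 2017, so the first patient could finish 2 weeks from about 1 November 2017. The stated completion date is 31 December 2019. From 18 October 2017 to 18 October 2019 is 730 days, and a further 74 days (13 + 30 + 31) reaches 31 December 2019, which gives 804 days. Subtracting the 14 treatment days leaves 790 days. If that date marks the end of data collection, an offer held until the analysis was finished would reach the earliest placebo patients at least 790 days after their treatment ended. The wording in Interventions does not suggest such a wait, although it does not rule one out.
6. **Effect on outcomes.** Outcomes and scans are collected only at baseline and after 2 weeks, and the offer is also placed after the 2 weeks. If a patient's assessment comes first, that patient's data are complete before the disclosure. If the offer comes first or at the same visit, the pain ratings, including the VAS for pain during the scan, could be given unblinded.

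The statements agree only if the offer waits until the analysis is complete, or if it does not distinguish the two capsule groups. The text says neither.

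**The case against.** The strongest reply is that the protocol never says the offer is made at the week-2 visit. It says that patients may choose after the 2 weeks, which sets an earliest time and names no visit and no person. An offer made after unblinding would fit all three sections. This is also a condensed article whose flowchart and schedule are not visible here, so missing logistics are not themselves a fault. Both points stand. They are why the conclusion is conditional and rests on the statements made rather than on absent detail. Deferral is still the less natural reading, given the interval shown above.

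A reader might draw three stronger conclusions that the documents do not support.

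- **That the primary outcomes are biased.** Nothing places the offer before the week-2 assessment, and no later outcome exists to be contaminated.
- **That assessors and analysts are unblinded.** The Blinding section separately blinds evaluators and statisticians, and Data analysis describes the statisticians for the clinical data as independent and blinded. They can stay blind if kept away from the offer. No section says that unblinded staff decide on head-motion exclusions.
- **That later allocations become predictable.** Randomization describes sequentially numbered, opaque, sealed envelopes handled by an independent assistant, and gives no block size. Predictability is speculative on that description.

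It would also go too far to say that blinding holds for no capsule patient. As written, it covers the treatment period.

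**Conclusion.** The concern holds in a limited form. On the natural reading, the promise that patients and researchers in the capsule groups remain unaware until the analysis is complete describes a property that the design does not have. If the offers precede the analysis, up to 36 placebo patients learn their own assignment, and all 72 planned capsule assignments become known to whoever administers the offers, while other patients are still being enrolled and assessed and the analysis scheme may not be settled.

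This rests on two assumptions: that the offer is made before the analysis is complete, and that it is confined to the groups named. Bias in a patient's own week-2 outcomes needs a third, that the offer comes before or during the assessment, and the documents do not establish it. The main damage is to the accuracy of the blinding claim and to the protection of research staff from knowledge of the code. The sections should be corrected because they conflict on the trial's only blinded comparison.

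**What to change.** Reconcile Randomization, Blinding and Interventions. Which groups are offered care is for the investigators; the blinding text and the logistics must match what they decide.

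1. State when the offer is made relative to the end of blinding.
2. If it is made before the analysis is complete, make it only after that patient's week-2 questionnaires and scan are completed and locked.
3. Handle it through the pharmacy code-holder, so that the code is not released to the study team.
4. State that evaluators, scan processors, statisticians and those who write the analysis scheme are not told who received the offer or what was chosen.
5. Limit the blinding statement to the people and period for which it holds. A pharmacy hand-off does not keep placebo patients blinded, nor those who then treat them if they know which groups are eligible, and the text should say so.

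The cost is revised wording and a hand-off to a code-holder who already exists, assuming that person can take on the task. No additional trial data are needed. Because the trial is already recruiting, the sponsor should also record which staff, if any, have learned assignments through offers made so far.

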### Concomitant medications

Patients will be instructed not to take any caffeine (such as tea and coffee) or have any other treatments for KOA during the study. In case of severe knee pain, ibuprofen (300 mg each capsule with sustained release) will be allowed as rescue medication and should be recorded in the knee pain diary. Patients are also asked to record the name, dose, date, and the exact time of the medications used and reported to the researcher if they take any regular medications during the trial.

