## Background

Non-steroidal anti-inflammatory drugs (NSAIDs), known as cyclooxygenase (COX) inhibitors, are often prescribed for the management of chronic and acute pain worldwide. NSAIDs exert analgesic effects by inhibiting COX activity in the arachidonic acid cascade and thus inhibit prostaglandin (PG) synthesis [1], which leads to a reduction or reversal of peripheral sensitization. Based on the results of animal studies, NSAIDs could also modulate pain intensity by suppressing prostanoid formation in the spinal cord and brain [2, 3], thus affecting central sensitization. On human beings, the peripheral action of NSAIDs for pain management had been well investigated. For instance, Gallelli et al. found that diclofenac, ibuprofen, and celecoxib can decrease tumor necrosis factor-alpha (TNF-α), interleukin-6 (IL-6), and vascular endothelial growth factor in the synovial fluid of the osteoarthritic joint with a parallel improvement in joint pain and function of patients [4]. However, the central action of NSAIDs is less studied, and the majority of these studies performed on healthy subjects or centered on acute pain condition. For example, neuroimaging studies found that instant NSAIDs could attenuate the activity on pain processing cerebral structures in healthy subjects [5] and top-down modulatory circuits in acute pain condition [6]. How the NSAID drugs acting on the central nervous system (CNS) in patients with chronic pain remains unclear and is worthy of further investigation.

Celecoxib, as the first COX-2 selective inhibitor, was introduced into clinical practice nearly 20 years ago [7–9] and widely used for many pain conditions for fewer side effects. It was reported that, compared with other NSAIDs such as ibuprofen and diclofenac at standard dosages, celecoxib was associated with a lower incidence of symptomatic ulcers and ulcer complications and other clinically important toxic effects [10].

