As a high prevalence chronic knee pain [11], the prevalence of radiographic knee osteoarthritis was 19% and 28% among adults over 45 years old in Framingham study and Johnston County Osteoarthritis Project [12]. With the aging of the population, most patients with KOA visit a doctor for their pain treatment [13, 14]. KOA has become the leading cause of disability in the world and brings an increasingly high social and economic burden [15, 16]. Meta-analysis has already indicated that celecoxib treatment (200 mg orally once daily) led to significant improvement in the pain and knee function of patients with osteoarthritis [17]. Although celecoxib treatment is effective for pain management in KOA, little is known about how celecoxib treatment modulates the activity of CNS to alleviate pain in patients with KOA.

With the application of neuroimaging techniques in pain research, investigators not only mapped the brain regions which are involved in the central pathogenesis of chronic pain but also can explore the cerebral responses elicited by analgesics so as to illuminate the central mechanism. With resting-state functional magnetic resonance imaging (rs-fMRI), investigators found that the patients with chronic pain demonstrated the alternations in functional connectivity (FC) of medial prefrontal-default mode network and the regional homogeneity (ReHo) value changes of anterior cingulate cortex [18–21].

These results greatly enhance the understanding of the central mechanism of chronic pain and provide a new approach to the research and development of drugs. For instance, Xiaoyan Chen et al. had shown that acupuncture can regulate the descending pain modulatory system of patients with KOA by enhancing the FC between the right frontoparietal network and medial prefrontal cortex [22].

So this trial aims to (1) investigate the influence of celecoxib treatment on the brain activities of patients with KOA compared with that of placebo treatment and waiting list by fMRI and (2) analyze the possible correlations between the changes of cerebral activity and the improvement of clinical variables in each group so as to explore how the celecoxib manages pain by modulating brain function to treat KOA.

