### Inclusion criteria

Inclusion criteria require that the patients (1) match the diagnosis criteria for KOA set by ACR in 1991 [23], (2) are between 40 and 60 years of age and are right-handed, (3) have not taken any pain killer medicine within 1 month, (4) have at least 3 months of knee pain duration, (5) have an average score on the knee pain Visual Analog Scale (VAS) of at least 3 cm (range of 0 to 10 cm) in the past 2 weeks, (6) have knee joint radiological degree of 0–II in accordance with the Kellgren–Lawrence scale [24], and (7) have signed a written informed consent form.

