### MRI data acquisition

MRI data will be acquired with a 3.0 T magnetic resonance scanner (GE 3.0 T MR750; GE Healthcare, Chicago, IL, USA) with an eight-channel phase-array head coil at the MRI Center in University of Electronic Science and Technology of China. Subjects will be asked to stay awake and to keep their heads still during the scan, with their eyes closed and ears plugged. Subjects will be asked to keep relaxed and not think anything particular during the whole scan. MRI scans will be assessed twice at baseline and after 2 weeks’ intervention or observation period for each patient.

Prior to the rs-fMRI scan, a high-resolution structural image for each subject will be acquired by using a three-dimensional MRI sequence (3DT1) with a voxel size of 1 mm^3^ employing an axial fast spoiled gradient recalled sequence (repetition time 6.008 ms, echo time 1.7 ms, data matrix 256 × 256, field of view 256 × 256 mm^2^). The rs-fMRI images will be obtained with echo-planar imaging (31 contiguous slices with a slice thickness of 5 mm, repetition time 2000 ms, echo time 30 ms, flip angle 90°, field of view 240 × 240 mm^2^, data matrix 64 × 64, total volumes 205). After the rs-fMRI scan, diffusion tensor imaging sequences with single-shot echo planar imaging will be acquired to detect the possible abnormality of the white matter with the following parameters: field of view 256 × 256 mm^2^, repetition time 8500 ms, echo time minimum, matrix = 128 × 128, slice thickness 2 mm, and 78 continuous axial slices with no gap. Two diffusion-weighted sequences will be acquired by using gradient values b = 0 s/mm^2^ and b = 1000 s/mm^2^ with the diffusion-sensitizing gradients applied along 64 non-linear directions.

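### Rescue ibuprofen is of celecoxib's own drug class and may be taken up to the second scan in every arm, which can pull the fMRI and in-scan pain contrasts toward no difference

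*Protocol article*

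**What the plan says.** Concomitant medications names the rescue drug: "In case of severe knee pain, ibuprofen (300 mg each capsule with sustained release) will be allowed as rescue medication". Use goes into the knee pain diary. The rule is addressed to patients in general. No arm is exempted, and no time before the second scan is excluded.

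The Background defines NSAIDs as COX inhibitors and places ibuprofen in the same class as celecoxib, "compared with other NSAIDs such as ibuprofen and diclofenac at standard dosages". On the brain it reports that "neuroimaging studies found that instant NSAIDs could attenuate the activity on pain processing cerebral structures in healthy subjects", cites a similar effect in acute pain, and says that the action in chronic pain is still unclear.

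The first aim is to "investigate the influence of celecoxib treatment on the brain activities of patients with KOA compared with that of placebo treatment and waiting list by fMRI". Patients must "have not taken any pain killer medicine within 1 month". Under MRI data acquisition, "MRI scans will be assessed twice at baseline and after 2 weeks" of treatment or observation. Under Outcome measurement, the primary pain measures include "average knee pain in the last 2 weeks and the VAS of knee pain during the MRI scan".

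**The concern.** The comparators are there to show what happens without the COX inhibitor. Baseline is free of pain killers by the entry rule, but the follow-up scan need not be. The imaging outcome is the change from before to after treatment, so an NSAID acting at the second scan in a placebo or waiting-list patient enters that change directly. If ibuprofen acts in the same direction as celecoxib, the difference between arms shrinks. The same holds for the VAS taken during the scan. If celecoxib relieves pain, severe pain and hence rescue should be commoner in the comparators, so the two arms would not cancel out. A null fMRI result would then be harder to interpret.

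The diary shows who took rescue and when. It cannot undo the bias. Rescue is taken after randomisation and is triggered by pain, so excluding or adjusting for users does not restore the randomised comparison.

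**Working it through.** **Inputs from the article.** 30 evaluable patients per group (Sample size); two-sided test at 0.05 (Data analysis); baseline free of pain killers for 1 month (Inclusion criteria). The stated enrolment reproduces as 30 × 1.2 = 36 per group, although 30/0.8 = 37.5, rounded up to 38, is the usual inflation for 20% dropout. The present point does not rest on that figure.

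**Not in the article.** Rescue rate, duration of ibuprofen's effect, effect size, SD and power. What follows is illustration under stated assumptions.

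**Per patient.** Let *q* be the share of comparator patients affected at the scan and *r* the ibuprofen effect relative to celecoxib, assumed 0.5 to 1.0. The share of the contrast retained is 1 − *rq*. One affected patient of 30 removes *r*/30 = 0.5/30 to 1/30 = 1.7% to 3.3%. A 10% loss needs *q* = 0.10/*r* = 0.10 to 0.20, that is, 3 to 6 of 30 patients.

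**Power.** Take the standardised effect that would give 80% power with 30 per arm, *d* = 0.736. The comparator mean shifts by *rqd* and its variance becomes 1 + (*rd*)²*q*(1 − *q*). Here *q* is the share who ever use rescue times the share of those still affected at the scan.

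| Ever use × still affected | *q* | Power, *r* = 0.5 | Power, *r* = 1 |
|---|---|---|---|
| none | 0 | 0.800 | 0.800 |
| 10% × 20% | 0.02 | 0.792 | 0.782 |
| 10% × 50% | 0.05 | 0.779 | 0.753 |
| 30% × 50% | 0.15 | 0.733 | 0.649 |

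Example for *q* = 0.15, *r* = 1: the contrast is 0.736 × 0.85 = 0.625 and the comparator variance is 1 + 0.736² × 0.15 × 0.85 = 1.069, which gives power 0.649.

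If celecoxib patients also take rescue, at half the rate and gaining 0.25 to 0.5 of *d*, the last row becomes 0.749–0.764 (*r* = 0.5) and 0.667–0.684 (*r* = 1).

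**Two-week average pain, for comparison.** Scale the effect by the share of days on which ibuprofen is used. With 10% using it on 3 to 7 of 14 days, power is 0.756–0.791. With 30% using it on 7 of 14 days, power is 0.657–0.735. Any equally effective analgesic would give the same figures, so this part does not depend on the drug's class.

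**The case against.** The strongest reply is that little ibuprofen will be taken. Rescue is for severe pain only and the period is two weeks. Patients have managed a month without pain killers and have Kellgren–Lawrence grade 0 to II. This stands, and it points to the upper rows of the table. It does not exclude use: entry sets a VAS floor of 3 cm with no ceiling, and other treatments for the knee are barred.

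Second, the imaging evidence cited concerns healthy subjects and acute pain, so an ibuprofen effect on these patients' scans is plausible but not shown. A substitute such as acetaminophen may also act on the brain. Both points stand. They make the choice of substitute less clear-cut and put more weight on the interval before the scan.

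Third, an interval before the scan and the analysis of rescue users are details that an article may leave to fuller documents. That is fair for the analysis. The choice of drug and the open permission to take it, however, are stated here, and no analysis plan can change what patients take.

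Three stronger readings are tempting, and the documents do not support them:

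- A reader might infer that the two-week average pain scores are compromised by the drug's class. Any effective rescue lowers those scores, so a change of drug would largely leave that exposure in place.
- A reader might infer a large loss of power by treating every rescue user as affected at the scan. Only patients in whom ibuprofen is still acting then are affected.
- A reader might see a contradiction with the Interventions section, which says: "Patients in the waiting list group will be observed for 2 weeks without any medical or other interventions". This reads naturally as no study intervention, subject to the rescue rule. It is at most a matter of wording.

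**Conclusion.** The point holds for the second scan. As written, the plan lets a drug of the class under test act in the comparators when fMRI and in-scan VAS are measured, after a baseline free of pain killers. The bias is toward no difference, provided that ibuprofen acts in the same direction as celecoxib and is used more in the comparators.

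The size is unknown and probably small. With 2% to 5% of comparators affected, power falls from an assumed 80% to 75%–79%. It falls to 65%–73% only if 15% are affected, with the lower figure requiring full equivalence to celecoxib. These figures rest on assumed rescue rates, relative effect and *d*. That rescue is open to all arms is inferred from the absence of any restriction. The trial remains interpretable, and the change is worth making because it is cheap and protects the central contrast.

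**What to change.** In Concomitant medications:

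- Ask for no rescue in a fixed interval before the second scan, with the length taken from the product label and the same rule in all three arms. Record each breach with its time and keep those patients in the primary analysis.
- Preferably name a rescue drug that is not an NSAID, for example acetaminophen, so that the comparators do not receive the class under test.

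Read the two-week average pain contrast as celecoxib versus comparator with rescue as needed, and add a sensitivity analysis from the diary. Keep patients already enrolled under the ibuprofen rule in the primary analysis, and flag them.

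The cost is one amendment during recruitment and, if the drug is changed, a different rescue supply. Some patients in severe pain will breach the interval. The substitute may have its own effect on brain activity, which the interval limits at the scan. Neither change protects the two-week average pain scores from rescue.
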